**Figure 3 fig3:**
[figure not shown]
Overview of the experimental intervention.

PNE sessions are divided into two content blocks: Block 1. *Knowing my painful process* and Block 2. *Pain self-management.* The Block 1 is divided into three sessions with the following educational topics: sessions (1–3) the concept of pain, acute pain and chronic pain, respectively; session (4) the concept of self-management in relation to pain and healthy habits; sessions (5–8) sleep, stress, diet and exercise habits in relation to chronic pain, respectively. A brief theoretical introduction to the GEM will be also given in the last session. A more detailed description of the content of all PNE sessions and the educational strategies to be followed is presented in the Supplementary material. Figure 4 shows an overview of the PNE programme.

**Figure 4 fig4:**
[figure not shown]
Overview of the PNE sessions.

GEM-Y sessions will be organised into four phases: theoretical content of the session, ‘pranayama’ or breathing exercises, ‘dhyana’ or guided meditation, and ‘asanas’ or postures and movements. Moreover, each session will focus on a different part of the body. In this way, yoga is used as a method of therapeutic exercise together with movement representation techniques (44, 45). The program will be delivered by a trained therapist following the principles of progression, gradualness and individualisation proposed by “Twin Peaks” metaphor (22). Thus, at the beginning of the sessions each participant must identify their pain baseline in order to apply an optimal dose of exercise (principle of individualisation). Instructions are given to the participants so that they can always adapt the level of effort to their needs and their progression (more functionality with less associated pain). With regard to the principles of progression and gradualness, since each participant will have a different starting point at the beginning of the programme and will move to their own level, the rate of progression of each participant must also be different. The intensity of the proposed exercises will be progressively adapted to the needs of the group by varying the following parameters: complexity of the ‘asanas’, volume of work (number of exercise blocks and repetitions), control of the relationship work time - rest time ratio. To identify the needs and progress of the group we will use the feedback collected from the participants at the end of each session, and the weekly pain diaries. A more detailed description of the GEM-Y sessions can be found in the Supplementary material.

The whole intervention will be implemented online using the videoconference platform of the University of Seville. Furthermore, WhatsApp and e-mail will be used during the study to give information, provide material or answer queries. Participants’ attendance will be recorded, along with the reasons for non-attendance.

Participants in the control group will only receive traditional biomedical information (26, 36), i.e., explanations of perceived pain based on tissue issues, and general oncological recommendations for analgesia. They will not receive any additional educational or movement-based intervention during the study period. They will be offered the content of the program after the follow-up period for ethical reasons. An online educational booklet will be provide to both groups.

### Method for data analysis

2.8

The statistical processing of the data will be conducted with the PASW Advanced Statistics, version 26.0 (IBM Corp, New York, NY, United States). Intention-to-treat principles will be considered for all analyses. The normal distribution of the variables will be assessed with the Shapiro–Wilk test. Descriptive data will be reported as mean (standard deviation), median (interquartile range Q_3_–Q_1_) or in percentages. Baseline homogeneity will be tested with Chi-square or Fisher’s exact tests; student’s t test or Mann–Whitney *U*-test.

In those variables in which the 4 measurements are adjusted to normality in both groups, a mixed-model analyses of variance ANOVA (2 × 4) will be used to differences in the outcomes after intervention, with group (PNE + GEM-Y or control) as a between-subject factor and time (the different measurements performed) as a within-subject factor. The hypothesis of interest will be the interaction group by time with an *a priori* alpha level of 0.05. Partial eta squared (η2) will be calculated to estimate the effect size. If any of the measurements do not adjust to normality, we will use the Friedman ANOVA test and the effect size will be calculated as Rosenthal’s r with the formula: *r* = Z/√N. All statistical tests will be performed considering a confidence interval of 95%.

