### Sampling method and sample’s size calculation

2.3

For sampling, non-probabilistic convenience and snowball methods will be used. The sample size was calculated based on the change in FACT-B score between the treatment and control groups at week 12. According to a previous study (30), it is estimated that patients in the intervention group would have a difference in FACT-B score of 10.11 points or more compared to the control group (*F*-value = 4.86). This difference is above the minimal important difference reported for this measure (7–8 points) (31) and results in an expected partial Eta2 effect size of 0.049. Considering 2 groups, 4 measurements, a type I risk or α 0.05, type II risk or β 0.20 (study power of 80%) and an estimated dropout rate of 15%, a total of 40 participants (20 per group) are needed to be enrolled. Sample size was calculated using the G*Power software, version 3.1.9.7 (Heinrich-Heine University, Düsseldorf, Germany). Figure 1 shows the flow chart of the study.

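### Intention-to-treat is claimed, but the stated 2 × 4 ANOVA and its Friedman fallback use only women with all four assessments, and no imputation is stated

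*Protocol article*

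**What the plan says.** Section 2.8 of the protocol article sets the principle: "Intention-to-treat principles will be considered for all analyses". Its next paragraph sets the method: "a mixed-model analyses of variance ANOVA" of 2 × 4 form, "with group (PNE + GEM-Y or control) as a between-subject factor and time (the different measurements performed) as a within-subject factor". The target is named: "The hypothesis of interest will be the interaction group by time". Partial eta squared "will be calculated to estimate the effect size". The ANOVA applies to variables for which all four measurements look normal in both groups. Otherwise: "If any of the measurements do not adjust to normality, we will use the Friedman ANOVA test". The abstract names the same 2 × 4 ANOVA, and section 2.8 names version 26 of the SPSS/PASW package.

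Section 2.6 schedules every outcome at T0, T1 (after four weeks), T2 (after twelve weeks) and T3 (three months later). Section 2.3 bases the sample size on the FACT-B difference at week 12 and allows for "an estimated dropout rate of 15" per cent in reaching 40 women. No section says how a woman with a missing assessment enters the analysis.

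**The concern.** A classical between/within ANOVA takes one row per woman with all four values. The repeated-measures procedure in SPSS drops the whole row if one value is missing, and Friedman's test needs complete rows too. Neither named route therefore retains every randomised woman, although the sentence before them promises intention-to-treat throughout.

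Two things are at stake. The first is the randomised comparison: exclusion after randomisation can unbalance the arms if the women excluded differ by arm in ways related to outcome. Section 2.5 says participants cannot be blinded. Section 2.7 asks one arm for 8 + 16 = 24 one-hour sessions, while the other arm gets information and a booklet. The second is waste: a woman who misses only T1 or T3 loses her week-12 score as well, and week 12 is the time point on which the sample size rests.

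**Working it through.** **1. Which analysis is meant.** The phrase mixed-model could suggest a likelihood-based linear mixed model, which keeps incomplete cases. The rest points to the classical mixed ANOVA: the 2 × 4 label, the between- and within-subject factors, partial eta squared, the normality condition on all four measurements, and a G*Power calculation in partial eta squared for two groups measured four times.

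**2. The plan's own sample size.** Inputs from section 2.3: partial eta squared 0.049, 2 groups, 4 measurements, alpha 0.05, power 0.80, dropout 15%. Not stated: the correlation between repeated measures (ρ) and the non-sphericity correction (ε).

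- f² = 0.049 / 0.951 = 0.0515, so f = 0.227.
- Group-by-time test: λ = f² × N × 4 × ε / (1 − ρ), df1 = 3ε, df2 = 3(N − 2)ε.
- ρ = 0.5, ε = 1: N = 28; 28 / 0.85 = 32.9, so 33 (34 in equal groups).
- ρ = 0.4, ε = 1, or ρ = 0.5, ε = 0.75: N = 34; 34 / 0.85 = 40.

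So 40 is attainable, but only with inputs the article does not give. In that reconstruction 34 is the number of women analysed; the 6 dropouts are simply replaced in advance.

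**3. Loss at the planned dropout.** 40 × 0.15 = 6 women excluded, 34 analysed. Complete cases use 34 × 4 = 136 of 160 planned assessments. If the 6 women each have 1 to 3 observed assessments, a mixed model uses 136 + 6 = 142 to 136 + 18 = 154.

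**4. Loss from missed visits.** The article gives no per-visit rate, so q is an assumption. T0 is taken as complete. Under independence, the expected number complete is 40(1 − q)³. If the same women miss all three follow-ups, it is 40(1 − q). If every miss falls on a different woman, it is 40(1 − 3q).

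| q per visit | Week-12 score observed | Complete, independent misses | Range from no overlap to full overlap |
|---|---|---|---|
| 5% | 38 | 34.3 | 34 to 38 |
| 10% | 36 | 29.2 | 28 to 36 |
| 15% | 34 | 24.6 | 22 to 34 |

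At 10% with independence, about 36 − 29 = 7 observed week-12 scores would be discarded.

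**5. Power for the interaction (ε = 1, ρ assumed).**

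| Women analysed | ρ = 0.4 | ρ = 0.5 |
|---|---|---|
| 40 | 0.88 | 0.93 |
| 34 | 0.81 | 0.88 |
| 28–30 | 0.72–0.75 | 0.80–0.83 |
| 24–26 | 0.64–0.68 | 0.73–0.77 |

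A mixed model that keeps partial data lies between the complete-case row that applies and the row for 40.

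**6. Bias.** This cannot be derived from the article. One illustrative simulation used 200 trials of 40 women with equal correlation 0.5. Dropout followed T1 in the programme arm only and was driven by a low T1 score, leaving 33.5 women complete on average. For a true T0-to-T2 difference in change of 0.50 SD, complete cases gave 0.49 and a mixed model 0.48 (standard error 0.03 each). Neither is detectably biased there: with equal correlations the T0-to-T2 change is uncorrelated with the T1 score that drives dropout. Other correlation patterns or dropout mechanisms need not behave this way, so the example shows only that exclusion need not bias the week-12 contrast.

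**The case against.** The strongest reply is that the article nowhere says complete cases or listwise deletion. Intention-to-treat with imputation before a repeated-measures ANOVA is a coherent plan, and an imputation rule may sit in a fuller document that is not shown. The principle may also mean only analysis in the assigned arm, which nothing in section 2.8 contradicts. This stands in part. A reader might infer that principle and method are incompatible; they are not, because imputation would join them. What remains is that the article fixes a method which, applied as written, does not deliver the principle it states.

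Other stronger readings are not supported either:

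- **That at least 6 women will be lost.** The 15% is a planning estimate, not a floor.
- **That 29 of 40 is the expected yield.** It rests on one assumed rate and on independence; misses that cluster in the same women leave more complete cases.
- **That the trial is underpowered for this reason.** At the planned dropout the allowance already covers the loss: 34 women give 0.81 to 0.88 under the assumed correlations. Power suffers only if misses exceed the allowance.
- **That dropout will differ by arm and relate to response.** This is plausible but not shown. Questionnaires are self-completed and separate from attendance, and controls are offered the programme after follow-up, which may help retain them.
- **That women who stop attending will stop being assessed.** No section says so.

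**Conclusion.** The concern holds in this form: section 2.8 claims intention-to-treat, but the ANOVA and the Friedman fallback, as usually run in the named software, analyse only women with all four assessments, and the article states nothing that would bring the others back. As written, the primary analysis is complete-case. The expected exclusion is about 6 of 40 women at the planned dropout, and about 34, 29 or 25 would be complete if 5%, 10% or 15% missed each follow-up independently.

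This rests on the classical reading of the ANOVA, which the text favours strongly, and on no imputation being applied first. The dropout allowance protects power among completers at the planned rate; it does not protect the randomised comparison. Bias is a plausible risk whose size and direction cannot be given.

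**What to change.** Replace the ANOVA with a likelihood-based linear mixed model: REML, fixed effects for group, time and group-by-time, a small-sample degrees-of-freedom correction, and every observed assessment of every randomised woman in her assigned arm. Alternatively, keep the ANOVA and pre-specify multiple imputation before it. Either choice brings the method into line with the stated principle. Report the complete-case ANOVA and a delta-adjusted analysis, which allows departures from missing at random, as sensitivity analyses. If neither change is made, the analysis should be called complete-case.

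The cost is small: analysis wording, slightly more work, no new data, and mixed models are available in the same package. There are two downsides. The mixed model, and standard imputation, assume data missing at random, so they do not by themselves deal with dropout that depends on unobserved outcomes; hence the delta-adjusted analysis. With the mixed model, partial eta squared gives way to an adjusted mean difference with its confidence interval, which can be read directly against the 7–8 point minimal important difference in section 2.3.

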### Group assignment and masking

2.5

This study will have two groups (experimental and control). For assignment, a random method will be carried out using an online tool called ‘random allocation software’ (2.0 version). A stratified allocation will be applied according to the women’s age (≤45 years old or >45 years old). On each of the strata, a randomization will be carried out by blocks of constant size. The assignment sequence will be hidden from the evaluator and the study subjects through an automated assignment system. The preparation of the sequence, the inclusion of the individuals in each group and the assignment of the treatments will be carried out by different members of the research team. On the other hand, the evaluator and statistician will be blinded. Nonetheless, the therapist and subject will not be able to be blinded because of the type of intervention.

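### The 2 × 4 ANOVA treats baseline FACT-B+4 as an outcome level instead of a covariate: a valid test that gives away precision, while the unused age stratum costs little

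*Protocol article*

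**What the plan says.** Section 2.8 (Method for data analysis) of the protocol article specifies a 2 × 4 mixed ANOVA for outcomes that pass the normality check, "with group (PNE + GEM-Y or control) as a between-subject factor and time (the different measurements performed) as a within-subject factor". The hypothesis of interest is the group-by-time interaction at alpha 0.05. Section 2.6 makes the pre-intervention assessment, T0, one of the four measurements. No covariate is named, and baseline is otherwise used only for tests of homogeneity between the groups.

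Section 2.5 (Group assignment and masking) states: "A stratified allocation will be applied according to the" age of the women, split at 45 years. It continues: "On each of the strata, a randomization will be carried out by blocks of constant size". The analysis section does not mention this stratum.

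Section 2.3 gives the basis of the sample size: "The sample size was calculated based on the change in FACT-B score between the treatment and control groups at week 12". It expects "a difference in FACT-B score of 10.11 points or more compared to the control group".

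**The concern.** Because T0 is one of the outcome levels, the interaction asks whether the group difference varies over T0 to T3. The part of it that concerns week 12 is the T2 difference minus the T0 difference. Randomisation makes the true T0 difference zero, but the model estimates it freely and carries its sampling noise into the treatment contrast. A baseline covariate would remove most of that noise.

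The trial enrols 20 women per arm and expects 15% dropout, so precision is scarce, and the baseline score is collected anyway. Age was thought important enough to stratify on, yet the analysis does not reflect it.

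The article states the factors, the number of levels and the hypothesis, so this concerns a stated choice and not a detail left to an analysis plan.

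**Working it through.** **Inputs from the article (section 2.3).** The calculation rests on "Considering 2 groups, 4 measurements", alpha 0.05, 80% power, 15% dropout, a difference of 10.11 points, partial eta squared 0.049, and 40 enrolled. Completers: 40 × 0.85 = 34, or 17 per arm.

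**Assumed, because the article gives no value.** Correlation r between visits, the FACT-B SD, the size of any age effect, and d = 0.45 at week 12. As a guide, f = √(0.049/0.951) = 0.227, and 2f = 0.454 if the effect size is read as a plain two-group comparison.

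**1. The plan's own figure.** For the within-between interaction, λ = f²·N·4·ε/(1−r), with 3ε and 3(N−2)ε df.
- r = 0.5, ε = 1: 28 completers, 28/0.85 = 32.9, so 33 enrolled.
- r = 0.4, ε = 1: 34 completers, 34/0.85 = 40.
- r = 0.5, ε = 0.75: 34 completers, 40 enrolled.

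The 40 can be reached but not confirmed from the stated inputs. It is taken as given.

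**2. Variance of the week-12 contrast** (equal variances s² at each visit). Change score: 2(1−r)s². Baseline as covariate: (1−r²)s². The ratio is (1+r)/2, a reduction of (1−r)/2.

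| r | ratio | SE reduction | 34 adjusted completers are worth |
|---|---|---|---|
| 0.4 | 0.70 | 16% | 34/0.70 ≈ 49 by change |
| 0.5 | 0.75 | 13% | 45 |
| 0.6 | 0.80 | 11% | 42 |
| 0.7 | 0.85 | 8% | 40 |
| 0.8 | 0.90 | 5% | 38 |

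The ratio is below 1 for every r below 1, so the direction does not depend on the assumption.

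**3. Week-12 power, like for like.** Noncentral t, 17 per arm, d = 0.45. The noncentrality is 0.45·√(17/2) = 1.312, divided by √(2(1−r)) for change (32 df) or by √(1−r²) with the covariate (31 df).
- r = 0.5: 1.312/1.000 = 1.31 gives 0.25; 1.312/0.866 = 1.51 gives 0.31.
- r = 0.7: 1.312/0.775 = 1.69 gives 0.38; 1.312/0.714 = 1.84 gives 0.43.

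**4. The planned 3-df interaction against a joint 3-df test of T1 to T3 adjusted for baseline.** Noncentral F, compound symmetry, 17 per arm, 10.11 points at each of T1, T2 and T3, about 95 denominator df for both tests.

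| SD | r | interaction | joint adjusted |
|---|---|---|---|
| 15 | 0.5 | 0.485 | 0.706 |
| 15 | 0.6 | 0.586 | 0.758 |
| 15 | 0.7 | 0.725 | 0.839 |
| 20 | 0.5 | 0.285 | 0.441 |
| 20 | 0.6 | 0.351 | 0.486 |
| 20 | 0.7 | 0.458 | 0.571 |

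With a cautious 31 denominator df, the adjusted test at SD 15 gives 0.66, 0.72 and 0.80, still ahead.

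**5. Age stratum** (4,000 simulated trials, 30% of women in one stratum, r = 0.6, effects in SD units).
- Age effect constant over time: the change-score SE is 0.304 with or without the stratum when the effect is 1 SD. The baseline-adjusted SE is 0.281 without and 0.276 with it.
- Age effect of 0.5 SD at baseline and 1.0 SD at T2: the change-score SE is 0.314 without and 0.304 with it (3% too large). The baseline-adjusted SE is 0.297 against 0.276 (8%). Type I error without the stratum is about 0.04 in both.

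**The case against.** The strongest reply is that nothing in section 2.8 is invalid. Under randomisation the planned test has the right type I error, and the sample size was framed for the same 2-group, 4-measurement layout. This stands: the point is about efficiency. A reader might infer bias or an invalid test, but the documents do not support that. Nor do they show that 40 is the wrong number, as step 1 indicates.

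Second, an age effect that is constant over time cancels from the group-by-time interaction. A reader might infer that leaving out the stratum makes the planned test's standard errors wrong by several per cent. That needs an age effect on the trajectory, and nothing in the article suggests one. This also stands.

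Third, baseline-adjusted power might be set against a plain comparison of week-12 scores, which at d = 0.45 appears to raise power from 0.25 to 0.44 at r = 0.7. The trial plans no such comparison. Against the change score, which is the week-12 part of the planned interaction, the gain is 0.38 to 0.43.

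Fourth, the (1+r)/2 ratio belongs to a single-visit contrast and does not carry over directly to a 3-df omnibus test. That is correct, and step 4 makes the comparison separately. An adjusted T2 contrast alone does not always beat the omnibus test. With an effect at T2 and T3 only, SD 15 and r = 0.5, it has power 0.59 against 0.62, and the gap is wider at r = 0.7 (0.76 against 0.85).

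**Conclusion.** The point holds as a matter of efficiency. The stated model treats baseline as an outcome and so loses 25% of the attainable reduction-free variance at r = 0.5, and 15% at r = 0.7, on the week-12 contrast: that is, the variance could be lower by those shares. In power at d = 0.45 this is 5 to 6 percentage points. For the omnibus question with equal effects at T1 to T3, the gain at r = 0.5 to 0.7 is about 11 to 22 points at SD 15 and 11 to 16 points at SD 20.

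The age stratum is secondary. Its absence costs the planned interaction nothing if age acts equally at all visits, and little otherwise. Once baseline is a covariate, leaving the stratum out makes standard errors slightly too wide if age predicts the outcome.

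The sizes rest on assumed r, SD, d and age effects, and on compound symmetry. The direction of the week-12 variance result does not depend on the value of r.

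**What to change.** Model FACT-B+4 at T1, T2 and T3 with group, visit, group-by-visit, baseline score, baseline-by-visit and the randomisation age stratum. Use the same form for each secondary scale with its own baseline.

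Replace the group-by-time hypothesis with a named treatment test, fixed before the data are seen:
- the adjusted group difference at T2, the time point on which the sample size rests, as primary; or
- a joint 3-df test of the group differences at T1, T2 and T3.

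Do not keep the group-by-visit interaction over T1 to T3 as the test. With T0 removed it asks only whether the effect differs between visits. For an effect equal at all three visits its noncentrality is zero, so its power is 5%.

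**Cost.** No extra women or visits. The model spends about 4 df (baseline 1, baseline-by-visit 2, stratum 1), and the analysis wording changes, including the hypothesis. The T2 contrast can have less power than the omnibus interaction when the effect is absent at T1. The joint adjusted test was at least as powerful in every scenario checked at about 95 denominator df, so it is the safer choice if a late effect is thought likely.

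### The sample size targets the week-12 FACT-B difference, but the primary test is an omnibus 3-df group-by-time interaction that can be significant with no week-12 effect

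*Protocol article*

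**What the plan says.** Section 2.3 of the protocol article states: "The sample size was calculated based on the change in FACT-B score between the treatment and control groups at week 12". It expects a "difference in FACT-B score of 10.11 points or more compared to the control group", notes that this exceeds the minimal important difference of 7–8 points, and says that it "results in an expected partial Eta2 effect size of 0.049". The remaining inputs are two groups, four measurements, alpha 0.05 and 80% power, with attrition put at 15%, giving 40 participants, 20 per group.

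Section 2.6.6 sets four assessments: T0 before the intervention, T1 after four weeks of pain neuroscience education (PNE), T2 after the complete 12-week programme, and T3 after three months of follow-up. Week 12 is therefore T2.

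Section 2.8 specifies a 2 × 4 mixed ANOVA in which every measurement is a level of the time factor. "The hypothesis of interest will be the interaction group by time", at alpha 0.05, and "Partial eta squared (η2) will be calculated to estimate the effect size". The abstract repeats the 2 × 4 ANOVA. The article names no week-12 contrast, no primary time point in the analysis and no baseline adjustment.

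**The concern.** The sample size is justified by one quantity: how far apart the groups are at week 12, in FACT-B points. The declared primary test asks whether the two mean profiles over T0–T3 differ in shape in any way. A small p-value would not show at which visit the groups differ, by how many points or in whose favour. Partial eta squared cannot be set against a threshold of 7–8 points.

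This matters in this design because T1 follows PNE alone, before the movement component starts, and T3 is follow-up. A significant interaction could come from a transient T1 effect or from a T3-only effect. The trial could then be reported as positive for the full programme without a difference at its end. Treating T0 as a fourth response, instead of as a covariate, also usually costs precision in a small trial.

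The article does state a primary hypothesis, so this is more than a detail left to an analysis plan that is not shown.

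**Working it through.** **Inputs from the article.** F = 4.86; difference 10.11 points; partial eta squared 0.049; 2 groups; 4 measurements; alpha 0.05; power 0.80; dropout 15%; 40 enrolled. Completers: 40 × 0.85 = 34, or 17 per arm.

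**Assumptions not in the article.** Correlation rho between visits of 0.3–0.7; compound symmetry; 4.86 is a 1-df two-group F; the implied SD is that of the raw score.

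**Standardised effect.** f² = 0.049/0.951 = 0.0515, so f = 0.227 and d = 2f = 0.454. The implied SD is 10.11/0.454 ≈ 22.3 points. The implied error df are 4.86 × 0.951/0.049 ≈ 94. That means about 96 participants, and 2√(4.86/96) ≈ 0.45 agrees.

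**The stated sample size.** For G*Power's within-between interaction, lambda = f² × N × 4 × eps/(1 − rho), with df 3·eps and 3·eps·(N − 2).
- rho 0.5, eps 1: N = 28, and 28/0.85 = 32.9, so 33.
- rho 0.4, eps 1, or rho 0.5, eps 0.75: N = 34, and 34/0.85 = 40.

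The article gives neither rho nor eps, so 40 is neither confirmed nor shown to be wrong. The calculation does have the form of the repeated-measures test; only its effect comes from week 12.

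**Degrees of freedom of the primary test.** (2 − 1)(4 − 1) = 3, with error df 3 × (34 − 2) = 96.

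**Power formulas.** Let p be the pattern of the group difference over T0–T3, scaled so that 1 is the full effect d.
- Interaction: lambda = (17/2) × d² × Σ(p − mean p)²/(1 − rho), noncentral F with 3 and 96 df.
- Week-12 ANCOVA: noncentrality = d × √(8.5/(1 − rho²)), t with 31 df, two-sided 0.05.

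**Effect at T1 only, none at T2.** p = (0, 1, 0, 0) and Σ(p − mean p)² = 0.75. With rho 0.6:
- d = 0.454: lambda = 8.5 × 0.2061 × 0.75/0.4 = 3.28; the interaction is significant in 29% of trials.
- d = 0.8: lambda = 8.5 × 0.64 × 0.75/0.4 = 10.2; 75%.
- A week-12 test rejects in 5% in both cases.

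An effect at T3 only gives the same figures under compound symmetry.

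**Effect present at T2, d = 0.454.**

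| Pattern at T1, T2, T3 | rho 0.3 | rho 0.5 | rho 0.6 | rho 0.7 |
|---|---|---|---|---|
| Interaction: 0, 1, 0 | 18% | 24% | 29% | 38% |
| Interaction: 1, 1, 1 | 18% | 24% | 29% | 38% |
| Interaction: ½, 1, 1 | 16% | 22% | 27% | 35% |
| Interaction: ½, 1, ½ | 13% | 17% | 20% | 26% |
| Interaction: 0, 1, 1 | 23% | 31% | 38% | 49% |
| Week-12 ANCOVA, any of these | 27% | 32% | 36% | 43% |

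In the first four patterns the week-12 contrast has more power throughout. In the last, the two are about equal at rho 0.5 and the interaction is ahead at rho 0.7.

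**The case against.** The interaction is a legitimate test of differential change under randomisation, and having baseline as a response level is common in this field. Section 2.3 speaks of change in FACT-B, which a group-by-time test does address, and it enters four measurements. The sample size and the analysis are therefore not wholly disconnected. Post-hoc contrasts and mean differences with intervals may also stand in a fuller document.

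All of this is fair. It narrows the point to the target effect and the declared hypothesis, but does not remove it: a test of any difference in profile still does not answer the week-12 question.

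Three stronger readings are tempting, and the documents support none of them.

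- **A reader might infer that the interaction always has less power.** It does not when the effect is absent at T1 and sustained at T2 and T3. That pattern is plausible here, because T1 follows education alone and section 3 reports earlier evidence of no quality-of-life effect of PNE. Likewise, a large contrast such as 66% versus 90% (1.0 SD at T2, rho 0.5) needs the effect halved at both T1 and T3. With no T1 effect and half at T3, the interaction has 81%.
- **A reader might infer an inflated type I error.** If correlation decays over time and no sphericity correction is applied, the rate is about 6–7%. The article does not say that a correction will be omitted, and that choice is commonly left to an analysis plan.
- **A reader might infer that 40 was computed for a week-12 test.** The four measurements entered argue against that.

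**Conclusion.** The point holds as a mismatch between the effect that justifies the sample size and the hypothesis declared primary. Followed as written, the primary test can be significant with no week-12 effect: about 29% of trials for a T1-only effect of 0.454 SD and 75% for 0.8 SD, against 5% for a week-12 test. The 0.8 SD case is nearly twice the planned effect and only illustrates the mechanism.

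The loss of power is usual, not general. At 0.454 SD it is about 13–38% against 27–43% for four of the five patterns examined, with parity or a reversal in the fifth at rho 0.5 or above.

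That the test has 3 df and no direction follows from the article alone. The percentages rest on 17 completers per arm, compound symmetry, the assumed correlations and a standardised effect derived from F = 4.86 and eta squared 0.049. If the implied SD is that of change or a residual SD, the power figures would differ.

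**What to change.** State in section 2.8 that the primary analysis is the between-group difference in FACT-B total at T2 (week 12), adjusted for baseline FACT-B. Use either ANCOVA or a linear mixed model on T1–T3 with baseline as covariate and terms for group, time and group by time. Report the difference in points with its 95% CI, and read it against the 7–8-point minimal important difference. Make the T1 and T3 contrasts and the omnibus interaction secondary, and align the abstract.

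The cost is wording, since all four visits are already planned. There are two downsides: the overall-profile test becomes secondary, and some power is lost if the effect starts only after T1 and then persists.

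The change does not by itself give 80% power. With a standardised effect of about 0.45, the week-12 ANCOVA needs 59, 50 or 40 completers per arm at rho 0.5, 0.6 or 0.7. After 15% dropout that is 118/0.85, 100/0.85 or 80/0.85, or 139, 118 or 95 enrolled, against 40 planned. The sample size therefore has to be considered separately.

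### For any outcome that fails a normality check, the only test named is Friedman's, which has no group factor and cannot test the stated group-by-time hypothesis

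*Protocol article*

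**What the plan says.** All of this is in section 2.8, Method for data analysis, of the protocol article.

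- Hypothesis: "The hypothesis of interest will be the interaction group by time", at alpha 0.05.
- Normality check: "The normal distribution of the variables will be assessed with the Shapiro–Wilk test". No threshold is given for this test in particular; the section closes with a general 95% confidence statement.
- Main path: the 2 × 4 mixed ANOVA applies "In those variables in which the 4 measurements are adjusted to normality in both groups".
- Fallback: "If any of the measurements do not adjust to normality, we will use the Friedman ANOVA test", and on that path "the effect size will be calculated as Rosenthal’s r with the formula" r = Z/√N.
- The only between-group rank test named is for baseline: "Baseline homogeneity will be tested with Chi-square or Fisher’s exact tests; student’s t test or Mann–Whitney" U.

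The primary outcome is FACT-B+4 (section 2.6), and nothing exempts it from the switch. The stated purpose (Introduction) is to compare the programme with usual care.

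**The concern.** The trial's question is whether change over time differs between the randomised arms. The mixed ANOVA answers it through the interaction term. Friedman's test has neither a between-subject factor nor an interaction. An outcome sent down the fallback path therefore has no named test of the hypothesis set out a few lines earlier in the same section. If that outcome is FACT-B+4, the primary randomised comparison is not specified.

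The effect size does not match the test either. Friedman's statistic over four measurements is a chi-square on 3 degrees of freedom, not a Z. The fallback sentence is thus inconsistent within itself as well as with the hypothesis.

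**Working it through.** **Inputs from the article.** Two groups, four timepoints, 40 participants (20 per arm), 15% dropout, so 20 × 0.85 = 17 per arm completing. Planned effect: partial eta squared 0.049.

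**Assumed inputs, not in the article.** Shapiro–Wilk at 0.05; equal correlation r between visits; the trends and skewness given below.

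**1. The plan's own figure.** N = 40 was sized for 2 groups × 4 measurements. With f² = 0.049/0.951 = 0.0515 and noncentrality f²·N·m/(1 − r), a correlation of 0.4 and sphericity give N = 34 (noncentrality 0.0515 × 34 × 4/0.6 = 11.7, power 0.81). Then 34/0.85 = 40. At r = 0.5 the same formula gives 28, or 33 after dropout. The article states neither the correlation nor the sphericity correction, so 40 is attainable but cannot be confirmed. The point here does not depend on it.

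**2. What each path tests.**

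| Path | Test named | Group factor | Tests group by time? |
|---|---|---|---|
| All cells judged normal | 2 × 4 mixed ANOVA | Yes | Yes |
| Any cell judged non-normal | Friedman, pooled | No | No |
| Any cell judged non-normal | Friedman, per arm | No (two separate tests) | No |

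The article does not say whether Friedman would be pooled or run per arm. Neither form tests the hypothesis.

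**3. How often the fallback is triggered.** There are 4 timepoints × 2 groups = 8 checks per outcome. If independent, with every distribution exactly normal, P(at least one rejection) = 1 − 0.95^8 = 0.337. By simulation with correlated visits and 17–20 per arm:

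- exactly normal data: about 30–36%;
- skewness −0.5 (reflected gamma, r from 0 to 0.8): about 47–60%.

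**4. What Friedman would show.** Simulated normal data, no group difference, both arms improving by 0.5 SD by T2. Friedman was applied to every simulated trial, not only to those failing a check. A dash means no figure is given for that setting.

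| Per arm | r | Friedman pooled significant | Friedman in one arm significant | Significant in experimental arm only | Interaction F significant |
|---|---|---|---|---|---|
| 17 | 0.5 | 67% | – | 23% | 4.8% |
| 17 | 0.7 | 91% | – | 25% | 5.3% |
| 20 | 0.5 | 76% | 45% | – | – |
| 20 | 0.6 | 85% | 51% | – | – |
| 20 | 0.7 | 95% | 67% | – | – |

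Over 17–20 per arm and r = 0.5–0.7, the ranges are about 67–95% pooled, 37–67% in the experimental arm, and 23–26% for significance in the experimental arm only. The true interaction is zero throughout.

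The reverse case, with opposite trends of ±0.5 SD and 17 per arm, is a pure interaction. Pooled Friedman is significant in about 3% of trials; the interaction F test is significant in 82% (r = 0.5) to 96% (r = 0.7).

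**5. Whether the switch is needed to protect the error rate.** With no effects, the 2 × 4 interaction test rejected in 4.3–5.3% of normal-data trials. Under marked skew (lognormal shape, sigma 0.5) it rejected in 4.8–4.9%.

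**The case against.** Several points against this have weight.

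- **The main path is sound.** The Abstract names only the mixed ANOVA, and the switch works outcome by outcome. With exactly normal data, the interaction test is still used for a given outcome in about 64–70% of trials (100% minus 30–36%). A reader might infer that the trial loses its randomised comparison outright. The text does not support that: the loss reaches the primary analysis only if FACT-B+4 itself fails a check.
- **The article is condensed.** An effect size needing a Z suggests that unnamed pairwise rank tests are intended, and follow-up detail may sit in a fuller document. That may explain the formula, but it does not repair the rule. The article does name a test for this path, and that test does not fit the hypothesis. Pairwise tests between visits would still be within-person.
- **Misreporting is not stated.** A reader might infer that a significant Friedman result would be presented as a treatment effect. The article says nothing about how it would be interpreted. The figures in step 4 show what the test responds to, not what the investigators will claim.
- **Checking normality cell by cell is not in itself an error.** Within-cell normality follows from the ANOVA model's own assumptions. It is also tempting to say that choosing the test from the data inflates the type I error, but the two-stage procedure was not simulated, so that is not claimed here.

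**Conclusion.** Wrong as written, and it must be fixed. The mismatch between the fallback test and the stated hypothesis follows from the text alone and needs no assumption. So does the conflict between a Friedman chi-square and r = Z/√N.

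The size of the risk does rest on assumptions. The roughly one-in-three trigger rate under exact normality depends on a 0.05 Shapiro–Wilk threshold and 17–20 per arm. The 47–60% rate also depends on the chosen skewed distribution. The Friedman rejection rates depend on the assumed common improvement and correlation, and are illustrations only. The supportable conclusion is that, on a path likely enough to matter, no named test compares the arms.

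**What to change.** In section 2.8, delete the Friedman fallback and r = Z/√N. State that the 2 × 4 group-by-time model, or an equivalent linear mixed model, will be used for every scale score whatever the normality pre-test shows. Where normality is doubtful, add a supporting analysis that keeps the group factor: a permutation or bootstrap test of the group-by-time effect, or a rank-based ANOVA-type interaction test. Report the between-group difference with its 95% confidence interval.

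A narrower repair would also cure the defect: keep the check, but replace Friedman with one of those group-preserving tests. Either way the cost is one paragraph, with no new data and no change to N = 40.
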